## Abstract

**Background:**

This protocol is for a study of a new program to improve outcomes in children suffering from chronic pain disorders, such as fibromyalgia, recurrent headache, or recurrent abdominal pain. Although teaching active pain self-management skills through cognitive-behavioral therapy (CBT) or a complementary program such as hypnotherapy or yoga has been shown to improve pain and functioning, children with low expectations of skill-building programs may lack motivation to comply with therapists' recommendations. This study will develop and test a new manualized peer-mentorship program which will provide modeling and reinforcement by peers to other adolescents with chronic pain (the mentored participants). The mentorship program will encourage mentored participants to engage in therapies that promote the learning of pain self-management skills and to support the mentored participants' practice of these skills. The study will examine the feasibility of this intervention for both mentors and mentored participants, and will assess the preliminary effectiveness of this program on mentored participants' pain and functional disability.

**Methods:**

This protocol will recruit adolescents ages 12-17 with chronic pain and randomly assign them to either peer mentorship or a treatment-as-usual control group. Mentored participants will be matched with peer mentors of similar age (ages 14-18) who have actively participated in various treatment modalities through the UCLA Pediatric Pain Program and have learned to function successfully with a chronic pain disorder. The mentors will present information to mentored participants in a supervised and monitored telephone interaction for 2 months to encourage participation in skill-building programs. The control group will receive usual care but without the mentorship intervention. Mentored and control subjects' pain and functioning will be assessed at 2 months (end of intervention for mentored participants) and at 4 month follow-up to see if improvements persist. Measures of treatment adherence, pain, disability, and anxiety and depression will be assessed throughout study participation. Qualitative interviews for mentors, mentored participants, and control subjects will also be administered.

**Trial registration:**

ClinicalTrials.gov NCT01118988.

## Background

Chronic intractable non-malignant pain, including such functional disorders as recurrent abdominal pain (RAP) and chronic daily headache, is now recognized as a significant problem in children and adolescents, with potential long-term impact on the child's physical, social, and academic functioning, as well as on the family as a whole. Estimates of children experiencing recurrent or continuous pain range from 25% - 45.5%, with the most common types of pain reported as headaches, abdominal pain, limb pain, and back pain [1,2]. Many such children apparently continue to function effectively, attending school and continuing normal activities, with medical intervention only for acute episodes. A smaller, but significant, number, however, find themselves unable to self-manage their pain. They become patients with chronic pain and disability, falling into a cyclical pattern of pain, impaired functioning in physical, school, social, and even family and self-care domains, "doctor-seeking" and over-utilization of medications, and psychosocial distress, including anxiety and depression [3].

Functional impairment, particularly in academic work and social participation, is likely to have long-term effects on the individual's quality of life, even aside from the possibility that pain and physical limitations may persist into adulthood. Several well-designed studies using quantitative measures have provided evidence that impaired functioning in children with chronic pain is strongly associated with psychosocial distress [4-6] and with lower quality of life [4,7-10]. In particular, children with *unexplained *chronic pain - pain not associated with an identified organic diagnosis - often report significant dysfunction in normal activities, such as schoolwork, sleep, family activities, and athletic activities [10]. Although impaired functioning is a major factor in lower quality of life for children with chronic pain, we still know relatively little about the prevalence and severity of functional impairment, why some children experience more limitations than others, and which treatment interventions are the most effective in improving function [11].

### Current Therapeutic Interventions

When chronic pain cannot be fully alleviated, the optimal goal is for the adolescent is to learn effective ways to continue functioning and to self-manage pain. Several therapeutic programs have been developed, based on theories of health behavior change, to assist the patient in this process [12]. The newer therapeutic programs, the most well-known and widely practiced of which is cognitive-behavioral therapy (CBT), seek to mediate behavioral change through cognitive relearning. CBT employs a number of methods - including psychoeducation about the nature of pain responses, identification and modification of maladaptive cognitions, and encouraging behavioral changes to reduce or eliminate avoidance of activities [13,14]. Numerous controlled trials have shown CBT to be effective for a variety of types of pain, including in the child and adolescent populations [14-19].

In addition to psychotherapy, other types of complementary and alternative medicine (CAM) practices have shown varying levels of efficacy for chronic pain. These include interventions such as Iyengar yoga for rheumatoid arthritis [20], and acupuncture for low back pain [21]. In a 2005 review of studies examining CAM treatments for chronic pain conditions in children, Tsao and Zeltzer [22] found hypnosis and guided imagery to be "efficacious" for recurrent pediatric headaches, and found acupuncture, biofeedback, creative arts, herbal therapy, homeopathy, and massage therapy to be either "promising" or "possibly efficacious" for a wide variety of pediatric chronic pain conditions. Furthermore, the authors found multiple modalities packaged together to be more efficacious.

A well-designed intervention, however, is not enough. Patient *motivation *is at least one of the critical factors in successful outcomes of this therapeutic model [14]. Jensen and colleagues have recently proposed a cogent general model that integrates the varied theoretical approaches to describe a dynamic process that pivots on this concept of motivation, or readiness to change. An individual's readiness to change, they argue, is essential to his/her ability to learn successful pain self-management through new behaviors. They suggest some clinical approaches for enhancing readiness and promoting change, including encouragement to practice self-management; allowing the patient to observe other pain patients practice self-management; support of positive beliefs and non-judgmental non-support of negative beliefs; and development of a plan to address real or perceived barriers; and they call for research into interventions along these lines to enhance motivation [12].

Another formulation recently proposed by Sharp stresses the patient's cognitive activity in appraising and evaluating his or her pain, and its ongoing and interactive effects on mood, behavior, and somatic focus [23]. The patient's initial response to the pain is a function of cultural beliefs, learning history, and current contingencies, he argues, but then is continually reinterpreted with ongoing events. In particular, anxiety about recurrent pain and avoidance of activity that might cause pain will help to perpetuate the patient's hypervigilance for signs of recurring pain (as described by Eccleston and Crombez [24]) and his/her perceived inability to manage the pain. Moreover, Sharp contends that this attitude of "learned helplessness" may be perpetuated by physicians who have failed to offer helpful treatment or even to confirm the physical reality of the patient's suffering. "That is, patients could start to believe that 'nothing has worked so far so why would any future treatment help?" [23] A patient who has reached this point is likely to have a negative assessment both of the benefits of pain self-management and of his/her own ability or self-efficacy to learn these skills, and will therefore show a lack of readiness to change.

While current interventions such as those mentioned above are known to be effective, adherence to recommended treatments in children with chronic health conditions is typically low [25]. Simons et al. [19] report only a 46.7% rate of "full adherence" (defined as completing the full recommended course of treatment or currently receiving the treatment) to a referral of cognitive-behavioral therapy for children with chronic pain, lower than adherence rates for other treatment modalities (i.e., medical and physical therapy referrals). The authors also assessed barriers to treatment among non-adherents and found that negative attitudes and beliefs regarding the recommended intervention to be the most frequently cited reason for not completing the recommended treatment. This finding suggests that determining methods to improve adherence to recommended treatments is a necessary step to improving pain and functioning in this population.

### Strategies for Adolescents: Peer Mentoring

Innovative strategies to promote pain self-management in *adolescents *with chronic pain may be especially needed, as this age group has shown great variance in motivation and adherence in studies of CBT-based therapies for other chronic health conditions. In fact, children of all ages demonstrate low rates of adherence to recommended treatments for chronic health conditions, ranging from 11% to 50% [25]. However, some researchers have reported that motivation and adherence can be enhanced if young people have the opportunity to interact with peers who model and reinforce adherent behaviors, and Varni et al. have argued convincingly for "the power of peer relationships and social supports in mediating adjustment to chronic malfunctions" [25,26].

Peer mentors most often work in programs designed to encourage desired social and preventive health behaviors, such as nutrition and tobacco abstinence [27], non-violence [28], sexual abstinence [29], or HIV prevention [30] in physically healthy children. In a low-income area of Chicago, for example, 19 self-selected adolescents aged 14-21 designed and presented violence-prevention lessons to 50 younger children (7-13) over an 18-month period. Post-intervention, the mentored children showed lower acceptance of violence after the intervention than a control group of 75 children [28]; 11 of the adolescents continued with the program and 3 entered college or employment. Peer mentorship has only been explored in a few instances within medical treatment programs. In a youth-run program in San Francisco, peer-mentor-advocates have effectively empowered young people infected with HIV (ages 26 and younger) to access needed services and to learn coping skills for living with the disease [31]. Peer support has also been the subject of several studies of adolescents with diabetes, where researchers have found that the support of friend-peers is a critical resource for diabetic teens, providing important social and emotional support, and that structured peer-group interactions *may *improve adherence to glucose self-monitoring and control [32-34]. Greco and colleagues reported a successful education and support group intervention with 21 diabetic adolescents (ages 10-18) and their best friends (4 sessions); both the patients and their friends demonstrated higher levels of knowledge about the disease and its care, and the patients reported a higher ratio of peer-to-family support [33]. Clemente has used ethnographic methods to document the informal peer-mentoring provided to children newly admitted to cancer treatment wards by peers who had been through several treatment cycles [35]. We contend that trained peer mentors, who have successfully learned pain self-management skills, are an effective and feasible choice to promote pain self-management in the adolescent chronic pain population because this intervention has the potential to relieve the sense of isolation, difference, and helplessness reported by the adolescents.

In this exploratory pilot study, we will finalize development of an innovative, manualized peer-mentorship program designed to provide modeling and reinforcement by peers to other adolescents with chronic pain (the "mentored participants"). The goal of the mentorship will be to encourage the mentored participants to engage in therapies that promote the learning of pain self-management skills and to support the mentored participants' practice of these learned skills during a two-month intervention period. The study will examine the feasibility of this intervention for both mentors and mentored participants, and, through a randomized, controlled design, will assess the preliminary effectiveness of this program for both short and longer term effects on mentored participants' pain and functional disability.

### Aims

1. To test the feasibility and acceptability of a peer-mentorship intervention in supporting and encouraging adolescents with chronic pain and pain-related functional disability (the "mentored participants") to participate and persist in an active skills-building therapy that teaches pain self-management skills.

2. To test the feasibility of training adolescents who have coped successfully with chronic pain (the "mentors") to offer support and reinforcement to their peers in a structured peer-mentorship intervention, based on a manualized protocol developed within a social learning model grounded in CBT principles.

3. To determine if the mentored participants with chronic pain show improved adherence to recommended skills-building therapies, compared to a usual care control group of adolescents with chronic pain immediately after the two-month peer-mentorship intervention and at two-month follow-up (four months from baseline).

4. To determine if the mentored participants with chronic pain show improvements in pain levels and pain-related disability, compared to a usual care control group of adolescents with chronic pain immediately after the two-month peer-mentorship intervention and at two-month follow-up.

### Hypotheses

We propose to test our hypotheses through a trial of a peer mentorship intervention, using trained adolescents who have successfully learned pain management skills as mentors. The mentors will help to relieve the adolescents' sense of isolation and difference by relating their similar experiences, provide models of successful skill learning and reinforce the mentored participants' participation in skill learning activities. We propose the following hypotheses:

1. Adolescents receiving the peer mentorship intervention will report better adherence to recommended therapies, as compared to adolescents who do not receive the intervention.

2. Adolescents with better adherence to recommended therapies will show more improvement in pain and pain-related disability 2 and 4 months after baseline than those with poor adherence.

3. Adolescents receiving the peer mentorship intervention will report decreased symptoms of anxiety and depression and improved pain coping skills, as compared to adolescents who do not receive the intervention.

## Methods/Design

### Sample

#### Mentored and Control Subjects

All potential participants must be patients of the UCLA Pediatric Pain Program. During the first visit (prior to being offered study participation), all clinic patients are given a thorough medical evaluation and are recommended specific therapies to help with various skills to manage their pain. Any English-speaking patient between the ages of 12 and 17 diagnosed with a chronic pain disorder at the UCLA Pediatric Pain Program, or referred with this diagnosis, is eligible to be a subject for the study. Participants must have access to a computer connected to the internet, as well as a telephone in order to participate in the mentoring and complete measures administered online. Other than age, the only exclusions are out-of-area patients seen for consultation only before referral back to local providers or patients with another physical or psychological condition that, in the judgment of the principal investigator (PI), would make it difficult to participate.

#### Mentors

Any English-speaking patient between the ages of 14 and 18 years who has been treated for a chronic pain disorder at the UCLA Pediatric Pain Clinic and has been actively involved in recommended therapies will be eligible to serve as a mentor. Participants must have access to a computer connected to the internet, as well as a telephone. The PI ([name]) will identify suitable mentors based on her assessment of the adolescent's maturity, emotional stability and verbal communication skills. Mentors will be compensated $12/session.

### Randomization

Participants recruited for the mentored or control portion of the study will be randomized using a block randomization procedure to assure equal sample sizes in the mentoring and control groups. Using this method allows the groups to have similar numbers of participants in each group at all times. Using a block size of 4, participants are assigned to the appropriate treatment condition as they enroll in the study until the block is completed. Then the following 4 participants are assigned based on the next block [36].

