### Intervention

Each mentored participant will be assigned to a peer mentor. Each mentor will work with no more than three subjects at one time; once all mentors have been assigned one to three subjects, recruitment will stop until the intervention cycle concludes. Cycles may be staggered depending on recruitment and mentor availability.

Each cycle will consist of 10 sessions of 30-60 minute phone calls conducted over a period of eight weeks. The mentor and mentored participant(s) will have two sessions per week for the first two weeks, and one session per week for the remaining six weeks. Current literature supports the use of an expanding-interval schedule of interventions (compared to a massed (single session) or uniform-interval schedule) with evidence that the expanding schedule may help to attenuate long-term recurrence of negative emotions [37]. Phone calls will take place on a secured, monitored conference call line so that no participants will exchange personal contact information. The time of all phone meetings will be scheduled by the research staff, based on availability of mentor and mentored participant(s) and will remain at a fixed time each week. Mentoring sessions will occur only during the scheduled times and mentored participant-mentor contact outside of the mentoring sessions will be specifically prohibited. During each session, participants will also be viewing a slide presentation at the time of the conference call, so that didactic information can be presented. This presentation has been developed by doctoral-level research staff. As previously mentioned, to ensure safety of all participants, a member of the research team will be monitoring all telephone calls. This individual will facilitate the discussion, only if necessary, as well as intervene in any potential safety concerns (e.g., discussion of suicidal ideation) or inappropriate behavior (e.g., bullying).

In an effort to increase adherence, mentored participants will be informed that if they miss two consecutive mentoring sessions, or miss three sessions total over the course of the intervention for non-emergency reasons, they will be removed from the study. Additionally, peer mentors who miss two mentoring sessions (for non-emergency reasons) will be removed from further participation as a mentor. Mentored participants will then be reassigned to a new mentor for the remaining sessions.

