### Statistical analysis

#### Sample size

##### Sample Size Determination and Power Analysis

The proposed sample size was calculated with two objectives in mind: 1) to remain realistic in terms of recruitment based on our anticipated patient flow and the proposed time frame; and 2) to ensure the power to detect significant group differences in the primary outcome measures. Based on our average patient intake of 8-12 new patients a month and the parameters of our existing population, we estimate that we will be able to recruit 3-4 per month in the target age group (12-17) to participate in this pilot study, or a minimum *N *of 50. About 70% will be girls, 30% boys. The majority will be non-Hispanic white, but about 33% will be from other ethnic groups or of mixed-race. The second objective in calculating the proposed sample size is to ensure adequate power (.80) to detect variable relationships (two-tailed, *p *< .05) when conducting the primary analyses. Since there have been no comparable studies of peer mentorship interventions and there are no data available to calculate effect sizes for adherence to skill-based therapies in a pediatric chronic pain population, we have chosen the conservative strategy of extrapolating from other studies of pediatric pain that have used the Functional Disability Inventory (FDI) [39] as an outcome measure in evaluating a CBT-based intervention, in making our power calculations. One study [45] included 30 adolescents with fibromyalgia randomized to either 8 weeks of coping skills training or control (self-monitoring) and then crossed-over to the alternate condition. For the FDI, the authors reported overall effect sizes of 1.29 for patients (n = 14) who received the self-monitoring first and then the coping skills training and 0.52 for patients (n = 13) who received the coping skills training followed by self-monitoring. A second study examined an 8 week CBT trial in 44 adolescents with fibromyalgia [46]. These authors found a significant reduction in the FDI following treatment compared to waitlist control, with an effect size of 0.75. Using the smallest effect size reported in these two studies (i.e., .52), which corresponds to a medium sized effect according to the conventions proposed by Cohen [47], with power of .80 to detect a significant difference in FDI scores using two-tailed tests and with alpha set at .05, it is estimated that we will be able to detect this effect size with 29 subjects per group.

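### A constant, published block size of 4 in a single-clinic trial with visible arms lets anyone who tracks past allocations know about one third of assignments in advance

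*Protocol article*

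**What the plan says.** The Randomization section describes a "block randomization procedure to assure equal sample sizes in the mentoring and control groups". It continues "Using a block size of 4, participants are assigned to the appropriate treatment condition as they enroll in the study" and, once a block is full, "Then the following 4 participants are assigned based on the next block". The size is thus constant and printed, and the allocation is 1:1.

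Four other statements bear on how visible the sequence is and where discretion lies:

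- **One source of patients.** Under Mentored and Control Subjects: "All potential participants must be patients of the UCLA Pediatric Pain Program". No stratification is described, so one running sequence is the natural reading.
- **Arms that cannot be masked from staff.** The abstract's Methods say "The control group will receive usual care but without the mentorship intervention". Under Intervention, "The time of all phone meetings will be scheduled by the research staff", and a team member monitors every call.
- **A discretionary exclusion.** Under Mentored and Control Subjects, a patient can be left out for another condition that, "in the judgment of the principal investigator (PI), would make it difficult to participate".
- **Slow accrual.** The sample-size section expects 3-4 recruits a month, so a block of 4 takes about a month to fill.

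**The concern.** With a constant block size, the boundaries fall after participants 4, 8, 12 and so on. Once two places in a block have gone to one arm, all its remaining places belong to the other arm. A person who knows the earlier allocations then knows the next one before the next adolescent is judged eligible or approached.

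This matters more here than in many trials. The study's rationale is that motivation drives adherence, and adherence is a primary outcome. If more motivated adolescents tended to enter when the next place was mentoring, the comparison would favour mentoring without any effect of mentoring. The planned adjustment would not reliably correct this. Under Preliminary Analyses, covariates enter only if they differ significantly between groups, and neither the listed measures nor Table 1 includes a measure of motivation or readiness.

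**Working it through.** The article states no predictability figure, so there is none to reproduce. The check uses block size 4, 1:1 allocation, one sequence, and the planned 29 per group (58 in all). The observer is assumed to know past allocations.

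**Certain allocations.** A 1:1 block of 4 has 6 equally likely orders. In 2 of them (AABB, BBAA) places 3 and 4 are both certain; in the other 4 only place 4 is.

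- Expected number per block: (2×2 + 4×1)/6 = 1.333.
- Share: 1.333/4 = 33.3%.
- At 58 participants there are 14 full blocks and 2 places over, and those 2 are never certain: 14 × 1.333 = 18.7, or 18.7/58 = 32.2%.
- At the article's minimum of 50 participants, one third is about 17. At 64-96 (32-48 per arm) it is about 21-32.

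**Best guess** (name the arm that is behind; toss a coin when tied). The chance of being right at places 1 to 4 is 1/2, 2/3, 2/3 and 1. The mean is 2.833/4 = 17/24 = 70.8%, against 50% under simple randomisation.

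**What steering could do.** Suppose there is no true effect and the enrolled patient's expected outcome is shifted by δ SD at each certain slot. Certain slots are split evenly between the arms, so with p = 0.322:

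- two-way steering (better prognosis before mentoring slots, worse before control slots): bias = 2δp;
- mentoring slots only: bias = δp.

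The standard error of the difference is √(2/29) = 0.263 SD. Type I error is from simulation of a two-sample comparison.

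| Assumed shift δ | Steering at every certain slot | Bias (SD) | Type I error |
|---|---|---|---|
| 0.25 | two-way | 2 × 0.25 × 0.322 = 0.16 | about 9% |
| 0.50 | two-way | 2 × 0.50 × 0.322 = 0.32 | about 21% |
| 0.25 | mentoring only | 0.25 × 0.322 = 0.08 | about 6% |
| 0.50 | mentoring only | 0.50 × 0.322 = 0.16 | about 9% |

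A normal approximation agrees for the first row: 0.161/0.263 = 0.61, so P(Z > 1.96 − 0.61) + P(Z < −1.96 − 0.61) is about 9%. Steering only half of the certain slots halves the bias. At δ = 0.25, two-way, it is then about 0.08 SD with a type I error of about 6%.

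**After the change.** Simulation at 58 participants, with equiprobable sizes and an observer who knows the set of sizes but not the boundaries:

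| Scheme | Certain | Best guess right | Largest momentary imbalance |
|---|---|---|---|
| Fixed 4 | 32.2% | 70% | 2 |
| Random 4/6 | 5.6% | 69% | 3 |
| Random 4/6/8 | 2.2% | 68% | 4 |

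Under two-way steering of the remaining certain slots, type I error is about 5-6% with either random scheme.

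**The case against.** The strongest reply is that the harm is conjectural. The article does not say that whoever judges eligibility or approaches families also holds the running sequence. The step from staff scheduling calls to recruiters knowing the next arm is an inference, and this stands. The exclusion is also narrow: it concerns another physical or psychological condition, and low motivation is not a ground for it. A reader might infer that enrolment is being steered, or that allocation concealment is absent. The article supports neither. Who holds the list and when each allocation is released are details that a condensed article commonly leaves to the full protocol.

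That reply does not dispose of the block size, which is a stated choice. Good list-keeping does not hide the last place in a known block of 4 from someone who has seen the first three filled.

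A second reply is that small blocks serve a purpose. The article wants similar group numbers at all times, each mentor takes at most three participants, and cycles are expected to bring in 4-6 mentored participants. This stands as a cost to be weighed.

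A third is that this is an exploratory pilot with a larger trial to follow, and predictable allocation leaves the feasibility aims untouched. That limits the consequence to the randomised comparisons of adherence, pain and disability, which the article nevertheless intends to test.

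**Conclusion.** The point holds as a weakness in a stated design choice. About one third of allocations (33.3% per full block, 32.2% at 58 participants) are certain in advance to anyone who tracks them. That figure is exact, given one sequence and knowledge of past allocations. That the arms are open to staff is inferred from what the arms are; the article does not use the term.

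The bias figures are conditional. The shift sizes are assumptions without a source in the article. The 0.32 SD and 21% are the upper corner, requiring a 0.5 SD shift in both directions at every certain slot. For scale, 0.32 SD is 62% of the planned effect of 0.52 (0.32/0.52), while the mildest full-steering case, 0.08 SD, is 15%. It would be wrong to read any of these as the trial's actual error rate.

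**What to change.** For blocks not yet used, replace the fixed block of 4 with randomly varying sizes, for example 4 and 6, or 4, 6 and 8, and do not disclose them to recruiting staff. This needs a new list for the remaining participants and one amended sentence in the Randomization section.

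The price is a looser running balance: at most 3 (4/6) or 4 (4/6/8) instead of 2, which slightly affects mentor scheduling. The 4/6 mix is the milder compromise if mentor capacity is tight.

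The change removes most of the certainty but little of the guessing, since best-guess accuracy falls only to about 69% or 68%. The sponsor should therefore confirm that the full protocol has the list held outside recruitment and each allocation released only after eligibility, consent and baseline are complete. If it already does, nothing more is needed on that side.
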